#### Participants

This study aims to recruit 500 women with an abnormal annual Pap test and follow-up scheduling for colposcopy at EFHC or PAC. Based on the current patient flow in the two clinics, we expect to randomize approximately 100 women from EFHC and 400 from PAC. Entry criteria will include women of age 18 or older who speak either English or Spanish and who have received an annual Pap test that warrants scheduling for colposcopy at EFHC or PAC. Women scheduled for a repeated Pap test or repeated colposcopy as follow up to a previous abnormality will not be enrolled because they may already have completed their initial information seeking process.

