##### Telephone calls to the CIS

The CIS will tabulate calls originating from the study. When CIS information specialists answer the telephone, they log call and caller information into a standard Electronic Call Record Form (ECRF). With the caller's consent, three customer service questions are asked of all callers:

1. Have you used our service before?

2. How did you find our number to call?

3. What is your home ZIP code?

The ECRF response field for Question #2, "How Found Out" (HFO) has many codes, e.g., 300 - TV, 400 - radio, 801- ACS etc., including blank codes that can be assigned to a specific promotion or research study. Four How Found Out response codes will be allocated to identify the conditions in this study: Code 1: PAC, Usual Care; Code 2: PAC, Intervention; Code 3: EFHC, Usual Care; Code 4: EFHC, Intervention.

Information specialists will follow a series of steps (see: ECRF programming below) to determine which, if any, of the four codes should be assigned to a call.

Operationalizing call tracking in this way produces de-identified data. Consequently, it will not be possible to link ECRF-coded call data to the patient's other individual level outcome data. To accomplish such linking, self-reported data on calls to CIS also will be collected from identified participants during the exit interview. This will allow exploratory examination of whether calling the CIS appears to mediate more timely follow-up and improved provider-patient interaction.

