##### Timely medical follow-up

Scheduling of colposcopy appointments will be tracked electronically and by exit interview. Timely medical follow-up will be operationalized by whether the patient keeps an appointment for colposcopy within six months of the initial abnormal Pap. Colposcopy is the primary disposition for abnormal Pap tests at EFHS and PAC. Clinic staff endeavor to schedule all patients within three months of the abnormal Pap. Colposcopy is performed on-site at both EFHS and PAC, in order to maximize continuity and follow-up. The procedure may be performed by the patient's primary care physician or by one of several doctors at each clinic who specialize in colposcopy.

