### Procedure and data collection

#### Protocol sequence

Clinic staff at both clinics will monitor Pap test results to identify patients eligible for this study. Based on patient flow data, we expect to be able to randomize approximately 100 women from EFHC and 400 women from PAC. Participants will be randomized to two conditions in which they will receive one of two letters previously described: Usual Care participants will receive the general reminder letter about their colposcopy appointment and Intervention participants will receive the reminder letter, plus a request to call the Cancer Information Service ([name]) and suggested questions to ask.

An in-person informed consent process will be undertaken at the colposcopy appointment. Upon arrival for the appointment, clinic staff will remind patients about the letter, inform them about the study, and ask if they are interested in further information. Those interested in further information will be approached by research staff and given a detailed description of the study, emphasizing that participation is completely voluntary. Participants who agree to participate and provide written consent will be enrolled in the study and will receive an exit interview.

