#### Statistical analysis

Based on information provided by site providers, we estimate a final N of 500 (250 intervention, 250 control) consented for follow-up to be reasonable and achievable within the one-year recruitment window. The study has four specific aims:

**Aim 1 **is to conduct focus groups about the CIS, and the targeted study letter with 10 patients and 10 providers from two large clinics that serve low-income women in Chicago. Transcripts of the focus groups will be analyzed qualitatively for content to determine the totality of ideas that emerge from the discussions. All data will be summarized descriptively. In particular, information will be compiled on familiarity with and views about the CIS, barriers and facilitators to telephoning the CIS for information about cancer prevention and screening and perceived information support needs for following up abnormal Pap tests.

**Aim 2 **is to randomize and enroll all women between ages 18-60 who receive an abnormal annual Pap test with follow-up scheduling for colposcopy at two clinics for underserved women. Randomization to Usual Care or Intervention will be conducted using the previously described procedure.

**Aim 3 **is to compare the number of telephone calls made to the CIS by patients randomized to Intervention versus Usual Care in order to test the hypothesis that a targeted physician mailing that asks patients to call the CIS and suggests questions will increase CIS call volume compared to Usual Care control. The outcome measure will be whether or not a study participant calls the CIS. Proportions will be compared between study groups using the Cochran-Mantel-Haenszel chi-square test [50]. With 250 persons per group, there is 80% power to detect a difference of a 5% call rate in the control group versus a 12% call rate in the intervention group. There is greater than 99% power to detect the anticipated difference of 5% in the control group versus 40% in the intervention group.

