**Aim 4 **is to compare the Intervention and Usual Care groups' medical follow-up in the 6 months after abnormal Pap test notification and exit interview data at Pap test follow-up. The two outcome measures will be the dichotomous variable of timely follow-up completion (yes, no) as well as the CAHPS satisfaction questionnaire. The proportion of participants completing follow-up within 6 months will be compared between study groups using the Cochran-Mantel-Haenszel chi-square test. It is anticipated that 450 participants will consent to participation. With 225 persons per group, there is 80% power to detect a difference between a 55% appropriate follow-up rate in the control group versus a 68% rate in the intervention group. There is 99% power to detect the anticipated difference of 55% in the control group versus 75% in the intervention group.

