To compare patient satisfaction between the two groups, the four-item CAHPS scale will be used where each item is coded 1 (never, sometimes), 2 (usually) or 3 (always). The sum of these four items will have a range of 4-12. If this range represents 4 standard deviation units, then a conservatively large estimate of the standard deviation is 2 units on the CAHPS 4-item scale. Anticipated sample size for the analysis of satisfaction data (given expected follow-up rates of 55% control and 75% intervention) is 293 (control N = 124, intervention N = 169). These sample sizes have 80% power to detect an effect size of 0.34, where effect size is defined as the mean difference between intervention and control, divided by the standard deviation. With an estimated standard deviation of 2, this effect size translates into a mean difference of 0.68 (.34 × 2). With these assumptions for the sample size, the study is powered to detect a consistent difference between the groups of one response category for one item. Before the satisfaction data are analyzed, participant characteristics will be compared between the control and intervention subsamples to determine any selection bias that may have occurred due to differential follow-up between the groups. Satisfaction data will then be analyzed using a two-factor analysis of variance, with clinic (EFHC versus PAC) as one between-subjects factor and study condition (Usual Care versus Intervention) as the other. The interaction term will determine whether the intervention effect is different between the two clinics. Any demographic characteristics found to be different between the groups will be included in this analysis as covariates. Other potential covariates are whether the physician is patient's usual provider, language barrier, availability of needed translation, and whether family members accompany the patient to the appointment. The intervention by ethnicity (Hispanic vs. African American) interaction will also be tested: prior studies neither support nor negate such interaction. For all power calculations, a two-tailed test and a Type I error rate of 5% is assumed.

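### Timely follow-up is sized on 450 consenting women, but consent is taken only at the colposcopy visit that is itself the outcome, and the Aim 4 analysis set is not defined

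*Protocol article*

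**What the plan says.** All places are in the protocol article.

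- **Randomised number** (Participants): "we expect to randomize approximately 100 women from EFHC and 400 from PAC", about 500 in total. Randomisation and mailing of the letters come before any consent.
- **Consent** (Protocol sequence): "An in-person informed consent process will be undertaken at the colposcopy appointment". Enrolment follows from it: "Participants who agree to participate and provide written consent will be enrolled in the study and will receive an exit interview".
- **Outcome** (Timely medical follow-up): "Timely medical follow-up will be operationalized by whether the patient keeps an appointment for colposcopy within six months of the initial abnormal Pap". The same section says that appointments are tracked electronically as well as by exit interview.
- **Consented number, first statement** (Statistical analysis, opening): "we estimate a final N of 500 (250 intervention, 250 control) consented for follow-up to be reasonable and achievable".
- **Consented number, second statement** (Statistical analysis, Aim 4): "It is anticipated that 450 participants will consent to participation". Power is then given for 225 per group: 80% for 55% versus 68%, and 99% for 55% versus 75%. Aim 3, on calls to the Cancer Information Service (CIS), uses 250 per group.
- **Satisfaction data** (Statistical analysis): "Anticipated sample size for the analysis of satisfaction data (given expected follow-up rates of 55% control and 75% intervention) is 293", split into 124 control and 169 intervention.
- **Mediation** (Telephone calls to the CIS): self-reported calls are collected in the exit interview, and "This will allow exploratory examination of whether calling the CIS appears to mediate more timely follow-up and improved provider-patient interaction".

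**The concern.** A woman who never comes for colposcopy is never asked for consent. A set of consenting women is therefore a set of attenders, and attendance is what the outcome measures. Aim 4 nevertheless reduces the 250 randomised per group to 225 on account of consent, and then expects 45% (control) and 25% (intervention) of those 225 not to complete follow-up. Those statements do not fit together unless many women consent at a visit made after six months.

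What is at stake is the population for one of three primary outcomes. If an analyst took the consent-based number as the definition of the analysis set, the comparison would be restricted by a post-randomisation event that the intervention is meant to change. The protection given by randomisation would be lost.

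**Working it through.** **Inputs.** 500 randomised, taken as 250 per group; follow-up 55% control and 75% intervention; 450 consenting, 225 per group; two-sided 5% test (all from the article). One assumption is added where marked: 90% of attenders consent, read from 450/500 and taken as equal in both arms.

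**1. The stated power reproduces.** Pooled normal approximation, with p̄ the mean of the two rates:

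power = Φ{ [ |p₂ − p₁|·√n − 1.96·√(2p̄(1−p̄)) ] / √(p₁(1−p₁) + p₂(1−p₂)) }

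- 55% vs 68%, n = 225: (0.13 × 15 − 1.96 × 0.688) / 0.682 = 0.88, power 81.1% (stated 80%).
- 55% vs 75%, n = 225: (0.20 × 15 − 1.96 × 0.675) / 0.660 = 2.54, power 99.5% (stated 99%).

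The arithmetic is sound. The question is which women the 225 are.

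**2. The 293 reproduces from the 450.** 225 × 0.55 = 123.75 and 225 × 0.75 = 168.75, giving 124 + 169 = 293. So 450 − 293 = 157 women are counted as consenting but not as seen at the visit where consent is given.

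**3. How many can be asked within six months.** 250 × 0.55 + 250 × 0.75 = 137.5 + 187.5 = 325. With 90% consent (assumption) this is 292.5, which happens to equal the 293 above.

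**4. What 450 or 500 would need.**

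- Average attendance is 65%. With no refusals, 450 timely consenters need 450 / 0.65 ≈ 692 randomised, and 500 need 500 / 0.65 ≈ 769.
- With 500 randomised and no refusals, 225 per group needs 225 − 137.5 = 87.5 of the 112.5 remaining control women (78%) and 225 − 187.5 = 37.5 of the 62.5 remaining intervention women (60%) to attend after six months. The rates among consenters would then be 137.5/225 = 61% and 187.5/225 = 83%, not 55% and 75%.

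**5. What each reading of the analysis set does to 55% versus 75%.**

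| Women analysed | Control | Intervention |
|---|---|---|
| All randomised | 55% | 75% |
| Consenters only, few late attenders | near 100% | near 100% |
| All except attenders who refuse (10% assumed) | 123.75 / (123.75 + 112.5) = 52.4% | 168.75 / (168.75 + 62.5) = 73.0% |

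**6. Power with all randomised women.** The same formula at n = 250 gives 85.0% for 55% vs 68% and 99.7% for 55% vs 75%.

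**7. Mediation.** Self-reported calls exist only for women who attended and consented. In that group the yes/no outcome of timely follow-up is almost always yes, so there is little for a mediator to explain.

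**The case against.** The strongest reply is that the article never restricts Aim 4 to consenting women. The word *participants* is used under Randomization and Protocol sequence for women who have been randomised and sent a letter, as well as for women who consent. The derivation of 293 keeps non-attenders in the denominator of 225 and treats attenders as a separate subsample for satisfaction, with its own check for selection bias. Electronic tracking is named as a source that does not depend on consent, and the outcome is a plain yes/no. On this view, all randomised women were meant, and 225 per group is simply a cautious number.

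Much of this stands. A reader might infer that the plan conditions a primary outcome on itself and that the contrast must vanish. The text does not support that as a certainty, because the consented set is an inference from the sample size basis. On the milder reading, the difference is 20.6 points against 20.0 planned. A reader might also infer that 450 consents cannot occur. Late attenders could consent, so at the article's rates 450 is implausible, not impossible. Nor is 293 itself a rival total: it belongs to the satisfaction analysis and follows from 450.

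What the reply does not remove is the conflict between sections. If all randomised women were meant, the cut from 250 to 225 for consent has no purpose, since Aim 3 makes no such cut. The selection-bias check covers satisfaction only. No sentence says that timely follow-up is analysed in everyone randomised. This is not a detail left to a fuller document, because the stated numbers and the stated consent procedure disagree.

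**Conclusion.** The point holds as an inconsistency in the consented numbers and an undefined analysis set for a primary outcome. At the article's own rates, about 325 of 500 women at most could be asked for consent within six months, against 450 in Aim 4 and 500 in the opening of the Statistical analysis section. The effect on the result depends on the reading: none if all randomised women are analysed, a shift of two to three points per arm if only refusing attenders are dropped, and loss of the contrast if only consenters are analysed and few women attend late.

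This rests on the 55% and 75% rates and 250 per group; the 52.4% and 73.0% figures also rest on an assumed 10% refusal, equal in both arms. The power calculation is not at fault: it reproduces, and it improves once the full randomised set is used. The mediation point is secondary, because that analysis is labelled exploratory and only its binary follow-up part is affected.

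**What to change.** 1. State that timely follow-up is analysed in all randomised women by assigned arm (250 per group), from the clinics' electronic records, and that a woman with no kept colposcopy appointment within six months counts as *no*, whether or not she consents to the exit interview.
2. Confirm with the IRB the basis for using the records of randomised women who do not consent.
3. Restate Aim 4 power at 250 per group: about 85% for 55% versus 68%, and 99.7% for 55% versus 75%.
4. Correct the consented numbers of 500 and 450. Give 500 as randomised, and about 293 as consented (assuming that 90% of attenders consent), used for exit-interview outcomes only.
5. Limit the exploratory mediation analysis to outcomes that vary among attenders, such as satisfaction with communication, and drop it for the binary timely follow-up outcome.

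The cost is a wording change and the IRB confirmation. No extra patients are needed. If the IRB did not allow use of non-consenters' records, the full randomised comparison could not be made as described, so this should be settled before the analysis set is fixed.

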#### Outcomes and measures

##### Primary outcomes

There are three primary study outcomes 1) telephone calls to CIS (call volume); 2) timely completion of medical follow-up (within 6 months); 3) patient satisfaction with doctor-patient communication at medical follow-up.

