##### Patient satisfaction with provider-patient communication

Satisfaction with provider-patient communication will be assessed by the *Doctors Who Communicate Well *scale from the 2.0 Adult Core Survey of the Agency for Healthcare Research and Quality's *Consumer Assessment of Health Plans Study (CAHPS*^®^) [45-47]. The CAHPS scale consists of four items asking the degree to which the provider: listens carefully, explains things understandably, shows respect, and spends enough time with the patient. Each item has 5 response options: never, sometimes, usually, always, I didn't see the provider. The scale's developers recommend collapsing responses to a 3-category distribution by combining "never" and "sometimes" into a single category [48] yielding a 1-3 range per item, where higher numbers indicate better care. Validated in both English and Spanish [45-47], the *Doctors Who Communicate Well *scale shows excellent internal consistency (Chronbach's alpha = .86) and predicts the rated quality of health care [45]. Patients will complete the CAHPS immediately after the follow-up visit for colposcopy.

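### Satisfaction is compared only among women who attend, attendance is expected to differ (55% vs 75%), and adjusting for observed imbalances does not restore the randomised comparison

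*Protocol article*

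**What the plan says.** The Primary outcomes section lists three outcomes, the third being "patient satisfaction with doctor-patient communication at medical follow-up". The section on satisfaction with provider-patient communication fixes when it is measured: "Patients will complete the CAHPS immediately after the follow-up visit for colposcopy". Under Protocol sequence, consent comes at the same visit, after randomisation and mailing: "An in-person informed consent process will be undertaken at the colposcopy appointment".

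The Statistical analysis section treats completed follow-up within 6 months as an outcome in its own right and anticipates 55% in control and 75% in Intervention; it also gives power for 55% vs 68%. The satisfaction sample is then derived "given expected follow-up rates of 55% control and 75% intervention", giving 124 control and 169 Intervention women. Of these it says: "These sample sizes have 80% power to detect an effect size of 0.34".

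The same paragraph anticipates selection from differential follow-up. Before the analysis, "participant characteristics will be compared between the control and intervention subsamples to determine any selection bias that may have occurred". Demographics that differ enter the two-factor analysis of variance as covariates. Further candidates are whether the physician is the usual provider, language barrier, availability of translation, and whether family came along.

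**The concern.** The analysis set for a primary outcome is defined by an event that happens after randomisation and that the intervention is designed to change. If the letter works on attendance as hoped, the Intervention sample contains women whose counterparts in the control arm stayed away. A difference in mean satisfaction then mixes any effect of the letter on the encounter with a difference in who was there to be asked.

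The planned adjustment reaches only what is measured. The background section on cervical cancer disparities links follow-up to low fear of pain, perceived benefit as against fatalism, and confidence that the provider will understand the patient's needs. None of these is a demographic, and the last lies close to what the CAHPS items ask about (listening, explaining, respect, time). A factor associated with attendance may therefore be nearly the same thing as the outcome.

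Two features of the rule add to this. Choosing covariates by observed imbalance among 124 and 169 women cannot show that selection is absent. And some candidate covariates are recorded at the visit: the Intervention letter invites the patient or someone she designates to call, so family accompaniment could itself respond to the letter. Adjusting for it could remove part of an effect or introduce a new distortion.

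At stake is whether a positive or a null satisfaction result can be attributed to the letter.

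**Working it through.** **Inputs from the Statistical analysis section:** 225 women per arm; attendance 55% vs 75% (or 55% vs 68%); SD 2 points; effect size 0.34 SD; two-sided 5%.

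**1. The plan's own figures.** 225 × 0.55 = 123.75 (124) and 225 × 0.75 = 168.75 (169), total 293, as stated. Standard error in SD units: √(1/124 + 1/169) = 0.118. Power at 0.34 SD is 81.8% (noncentral t) or 82.0% (normal approximation), against a stated 80%. The arithmetic is sound.

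**2. Women without a score.** 450 − 293 = 157 of 450 (35%): 45% of control and 25% of Intervention.

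**3. Share of added attenders.** At most 55% of women can attend under both letters, so among Intervention attenders the share *q* who would not have come under Usual Care is at least (0.75 − 0.55)/0.75 = 26.7%. At 55% vs 68% it is 0.13/0.68 = 19.1%. If the letter deterred some women, *q* would be larger.

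**4. Effect on the test.** Let *d* be the satisfaction gap, in SD, between added attenders and women who would attend anyway. The documents give no value, so a range is assumed. I take *q* at its minimum and assume that the covariates remove none of the bias.

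- Bias = *q* × *d*
- Variance of Intervention scores = 1 + *q*(1 − *q*)*d*²
- SE = √(1/124 + variance/169)
- False-positive rate (letter changes no woman's satisfaction) = 1 − Φ(1.96 − bias/SE) + Φ(−1.96 − bias/SE)
- Power when the bias opposes a true 0.34 = Φ((0.34 − bias)/SE − 1.96)

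For *d* = 0.5: bias 0.267 × 0.5 = 0.133; variance 1 + 0.267 × 0.733 × 0.25 = 1.049; SE 0.1195. The false-positive rate is 20%. Power is Φ(0.207/0.1195 − 1.96) = Φ(−0.23) = 41%.

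| Assumed gap *d* (SD) | Bias, SD (points) | False-positive rate | Power at 0.34 SD if opposed |
|---|---|---|---|
| 0 | 0 | 5% | 82% |
| 0.25 | 0.07 (0.13) | 9% | 64% |
| 0.5 | 0.13 (0.27) | 20% | 41% |
| 1.0 | 0.27 (0.53) | 58% | 9% |

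At 55% vs 68% (225 × 0.68 = 153 in Intervention, *q* = 0.191), the same formulas give biases of 0.05, 0.10 and 0.19 SD and false-positive rates of about 7%, 12% and 33%. Power falls from about 80% to 67%, 52% and 22%.

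**5. Trimming bounds.** These bound the effect in women who would attend under either letter, by removing the top or bottom fraction *q* of Intervention scores. For a normal outcome, and assuming that the letter deters nobody, the mean shifts by φ(z)/(1 − *q*), where z is the 1 − *q* quantile.

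- 55% vs 75%: 0.329/0.733 = ±0.45 SD (±0.90 points)
- 55% vs 68%: 0.272/0.809 = ±0.34 SD (±0.67 points)

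The first exceeds the 0.34 SD (0.68 point) target; the second about equals it.

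**The case against.** The strongest reply is that the authors have seen the problem. They name selection from differential follow-up, compare characteristics in general, adjust for demographics that differ, and list further covariates. They also define the outcome at the follow-up visit and reduce the analysed sample to attenders. A reader might infer that the plan ignores selection or claims a satisfaction effect in every woman randomised; the text supports neither. What remains is narrower: the stated rule reaches measured differences only, and the Discussion still presents satisfaction as part of the efficacy test while its limitations do not mention this one.

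A second reply is that sensitivity analyses are commonly left to a full protocol or SAP that is not shown. That is fair for their mere absence. Here, though, the article fixes a method for the selection problem, and it is that method which is insufficient.

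Third, the gap *d* is assumed, no passage shows that added attenders differ in satisfaction, and the planned covariates might remove some of any bias. All of this stands, and it is why a range is shown. The bounds also use a normal approximation for a discrete 4 to 12 sum; the real ones would come from the observed scores.

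Finally, satisfaction with a visit does not exist for women who never attended, so no analysis can recover a mean for all women randomised. That is correct, and it limits what any fix can do.

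**Conclusion.** The point holds. On the plan's own attendance rates, at least 27% of Intervention attenders (19% at 55% vs 68%) would not have attended under Usual Care, and covariates picked by observed imbalance do not make the two attending groups comparable. That share follows from the stated rates alone. The error rates and power figures depend further on the assumed gap of 0.25 to 1.0 SD and on the covariates removing none of the bias.

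It would go too far to say that the satisfaction result will be biased, or in which direction, or that success on attendance must make it worse. This depends on whether the added attenders differ in satisfaction, which the document does not show. The supportable conclusion is that a satisfaction difference of the target size could not by itself be attributed to the letter, since the trimming bounds match or exceed that target. The sample size and power arithmetic is not in question.

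**What to change.** In the satisfaction paragraph of the Statistical analysis section:

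- Replace selection of covariates by observed imbalance with a short, prespecified list of baseline covariates. Do not adjust for visit-time variables that the letter may affect, such as family accompaniment.
- Prespecify either trimming bounds for women who would attend under either letter, with the assumption that the letter deters nobody stated, or a tipping-point analysis showing how different the added Intervention attenders would have to be to overturn the result.
- Word the satisfaction conclusion as a non-randomised comparison among women who attended and consented, and add this to the limitations.

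Inverse-probability weighting is not a good substitute. It too covers only measured selection, it targets a mean in all randomised women that does not exist for a visit-based outcome, and it needs records of women who never consented.

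The cost is a little more analysis and no new data. The real price is that the bounds may be too wide to support a firm conclusion on this primary outcome.

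### The satisfaction power of 80% fits a two-group comparison; in the planned clinic-by-condition ANOVA it is about 82% or about 63%, depending on a clinic weighting the protocol leaves open

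*Protocol article*

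**What the plan says.** All of this is in the Protocol article, mostly under Statistical analysis. The number expected for the satisfaction analysis "is 293 (control N = 124, intervention N = 169"), and of it the article says: "These sample sizes have 80% power to detect an effect size of 0.34". Effect size is defined there as the intervention-minus-control mean difference over the standard deviation. With an assumed SD of 2, 0.34 becomes 0.68 points on the four-item sum. The error rate is common to all outcomes: "For all power calculations, a two-tailed test and a Type I error rate of 5% is assumed".

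The analysis is then described: "Satisfaction data will then be analyzed using a two-factor analysis of variance, with clinic (EFHC versus PAC) as one between-subjects factor", and study condition as the other factor. The article adds: "The interaction term will determine whether the intervention effect is different between the two clinics". A condition-by-ethnicity interaction and several possible covariates are also planned. The Study Design section calls the trial a 2 × 2 factorial of clinic and letter.

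The clinics differ greatly in size. Under Participants, "we expect to randomize approximately 100 women from EFHC and 400 from PAC".

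The power statement mentions neither clinic nor interaction, and no section says how the two clinic-specific effects are combined into the condition main effect.

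**The concern.** In a balanced 2 × 2 layout the condition main effect is one quantity. With clinics of unequal size and the interaction in the model, it is not. A Type III test averages the two clinic-specific differences with equal weight, so EFHC, with about a fifth of the women, supplies half of the estimate and most of its variance. A Type II test, or a model with condition and clinic only, weights each clinic by the information it carries.

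Both are standard ways to read the main effect of a two-factor analysis of variance, and the stated power holds for only one of them. At stake is the power of a primary comparison. There is also a question of pre-specification: two main-effect tests of the same data would be available, and nothing in the article says which one counts.

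**Working it through.** **Inputs from the article.** Consent: "It is anticipated that 450 participants will consent to participation", so 225 per group. Attendance: "given expected follow-up rates of 55% control and 75% intervention". Two-sided alpha is 0.05, the effect size 0.34 and the SD 2. The clinic split is 100:400, that is 20:80.

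**Assumptions.** The 20:80 split holds among the analysed women in both arms, and the true effect is 0.34 SD in both clinics.

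**1. The stated figure.**
- Sample sizes: 225 × 0.55 = 123.75 and 225 × 0.75 = 168.75, matching 124 and 169.
- SE in SD units: √(1/124 + 1/169) = 0.1182.
- Non-centrality: 0.34 / 0.1182 = 2.88.
- Power from the non-central t with 291 df: 81.8%. The effect detectable at exactly 80% is 0.332.

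The stated 80% at 0.34 is therefore reproduced.

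**2. Cells of the planned model.** EFHC has about 25 control and 34 intervention women; PAC has about 99 and 135. The variances of the clinic-specific differences, in SD² units, are:
- EFHC: 1/25 + 1/34 = 0.0694
- PAC: 1/99 + 1/135 = 0.0175

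**3. The two main-effect tests** (289 residual df, true effect 0.34 in both clinics).

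| Contrast | SE formula | SE | 0.34 / SE | Power | Effect detectable at 80% |
|---|---|---|---|---|---|
| Information-weighted | 1/√(1/0.0694 + 1/0.0175) | 0.118 | 2.88 | 82% | 0.332 |
| Equal-weight | ½ √(0.0694 + 0.0175) | 0.147 | 2.31 | 63% | about 0.415 |

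At SD 2, 0.415 is 0.83 points, against the stated 0.68. A simulation of 20,000 data sets gave 81.6% and 63.4%.

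**4. Where the loss comes from.** With the same arm ratio in both clinics, and a share p of the women at EFHC, equal weighting multiplies the variance by 1/[4p(1 − p)]. At p = 0.2 this is 1/(4 × 0.2 × 0.8) = 1.56, equivalent to 293 / 1.56 = about 188 women. At p = 0.5 it is 1, and the two tests agree. The information-weighted test shows no practical loss at any split.

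**5. Sensitivity of the equal-weight power.**

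| EFHC:PAC split | 10:90 | 15:85 | 20:80 | 25:75 | 30:70 | 50:50 |
|---|---|---|---|---|---|---|
| Power at 0.34 | 41% | 53% | 63% | 70% | 75% | 82% |

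If clinic and covariates explain 10%, 20% or 30% of the variance, equal-weight power at 20:80 is 68%, 73% or 78%. The same reduction helps the information-weighted test, so the variance ratio of 1.56 between them stays.

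**6. The interaction itself.** Its SE is √(0.0694 + 0.0175) = 0.295. Power for a between-clinic difference of 0.34 SD is about 21%.

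**The case against.** The case against rests on four points.

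- **The article never chooses equal weighting.** This is correct. A reader might infer that the planned ANOVA as such delivers 63% power, or that the interaction term or the clinic imbalance causes the loss. The documents do not support this: a Type II test from the same fitted model keeps about 82%. Nor can the choice be read off the software. The section on quality control and data management names SPSS only for the study databases, not for an analysis procedure or a type of sums of squares.

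- **The stated 80% is not an arithmetic error.** This also stands. Effect size is defined as a two-group quantity and the power is computed correctly for it.

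- **The article's looser claim survives.** It says the study can detect a consistent shift of one response category on one item. That is 1 point, or 0.5 SD at SD 2. Even under equal weighting 0.5 / 0.147 = 3.39, which gives about 92% power. Only the sharper claim (0.34, or 0.68 points) depends on the weighting.

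- **The type of sums of squares is detail for an analysis plan, and the weighting is a choice of estimand.** This stands in part. A missing detail alone would not be a finding in a condensed article. But here the article states both a power figure and a model, and the figure is assured under only one reading of that model. If the effect differs between clinics, the two contrasts do answer different questions, and the information-weighted one is about 80% PAC. That is a reason to name the contrast in advance. The other two primary outcomes are tested by Cochran-Mantel-Haenszel, which weights strata by their size and arm split, not equally (the article does not name the strata). Information weighting for satisfaction would be in line with that.

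**Conclusion.** The power statement is correct for a two-group comparison but does not carry over to every reading of the planned analysis. At effect size 0.34 the condition main effect has about 82% power if it is information-weighted and about 63% if the clinics count equally, a gap of about 19 percentage points on a primary outcome. Both figures assume a constant effect across clinics and a 20:80 split among the 293 analysed. The equal-weight figure moves to 53% at 15:85 and 70% at 25:75. The documents do not show that the lower figure will apply. They leave it open, and it can be closed in advance at no cost. The point is a worthwhile improvement and not a mistake in the sample-size calculation.

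**What to change.** In the Statistical analysis section, name as the primary satisfaction test the condition effect from an additive model with condition and clinic, plus any planned covariates. State that condition-by-clinic and condition-by-ethnicity will each be tested in a separate secondary model. The low power of the clinic interaction suits it to that role. The existing power statement then stands as written.

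If the equal-weight main effect from the interaction model is preferred as primary, say so and restate the effect detectable at 80% power as about 0.415 SD (0.83 points at SD 2), with the assumed clinic split.

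Either change takes one or two sentences, to be settled before outcome data are examined. Neither needs more participants, other data or a change in trial conduct.
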